### Sample size estimates

Formal power calculations were conducted using parameters from Chinese population studies. Based on the Health Study of Chinese Shanghai Women reporting a 1.45-fold stroke risk increase with high parity (≥ 5 pregnancies), we calculated a requirement of 268 ASPP cases and 804 matched controls (1:3 ratio) to detect similar associations (*α*= 0.05, 80% power) [15]. For longitudinal analysis of stroke recurrence, 456 ASPP cases are needed to identify a 40% risk reduction (90% power), anchored to China-specific stroke incidence data. Our target enrollment of 400 ASPP patients balances statistical rigor and feasibility, accounting for a 20% attrition rate, multicenter recruitment capacity (36 centers, ~ 11 cases/center/year), and subgroup analyses (e.g., cerebral venous thrombosis).

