**Design:**

This study is a retrospective, observational, nationwide, multicenter research project planned to include 400 ASPP patients from 36 centers across 22 provinces in China, from 2015 to 2024. ASPP is defined as acute ischemic or hemorrhagic stroke during pregnancy or within 6 weeks postpartum, confirmed by neuroimaging. Two matched groups will be included for comparison: 400 pregnant/puerperal participants without a stroke history and 400 nonpregnant/puerperal participants with a recent stroke, matched by age and/or stroke etiology.

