Grouping of non-ASPP participants is as follows:Non-ASPP participants include two matched control groups: The first group consists of participants in the pregnancy or postpartum period without a history of stroke (pregnancy/postpartum non-stroke group); the second group consists of nonpregnant or non-postpartum participants who have recently experienced a stroke (nonpregnant stroke group).Matching criteriaFor the pregnancy/postpartum non-stroke group, controls will be matched to ASPP cases in a 1:1 ratio based on age (±2 years) and hypertension history, with the latter stratified into preexisting hypertension, pregnancy-induced hypertension, or no hypertension.For the nonpregnant stroke group, a 1:1 matching strategy will be applied using age (±2 years), stroke etiology (classified by TOAST criteria), and preexisting hypertension status.Classification of pregnancy-related etiologies is as follows:Postpartum vascular diseasePregnancy-related hypercoagulable statesPregnancy-induced hypertensionPreeclampsiaAmniotic fluid embolismMatching of nonpregnant/postpartum patientsAge matching (±2 years)Matching based on stroke etiology, such as cardiogenic stroke, atherosclerotic stroke, small vessel disease stroke, and other identifiable causes (e.g., intracerebral hemorrhage)Health status and comorbidities, including common comorbidities such as cardiovascular disease, hypertension, and diabetesLifestyle factors, such as smoking and alcohol consumption historyDiscussion of the impact of pregnancy-related etiologiesEtiological characteristics, such as thrombosis resulting from pregnancy-related hypercoagulable states, hemodynamic changes caused by postpartum vascular disease, and hypertensive lesions associated with preeclampsiaPhysiological changes: Physiological changes during pregnancy, such as increased blood volume, blood pressure fluctuations, and alterations in coagulation mechanismsPsychological and social factors: Assessing the unique challenges faced by pregnant women in coping with stress, anxiety, and other mental health issues, as well as their potential impact on stroke occurrenceImpact assessment: When comparing ASPP patients with nonpregnant stroke patients, the influence of pregnancy-related etiologies on stroke recurrence rates and long-term prognosis will be clearly delineated.

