### Statistical analysis

Descriptive statistics will express continuous variables as means (±standard deviation) or medians (interquartile range) and categorical variables as proportions. Chi-square tests or Fisher’s exact tests, along with Student’s *t*-tests or Wilcoxon rank-sum tests, will be used to compare demographics and clinical characteristics between cases and controls. Chi-square tests will compare dichotomous outcomes, while *t*-tests or Mann-Whitney *U*-tests will compare quantitative outcomes. Kaplan-Meier curves and log-rank tests will evaluate survival analyses, with Cox proportional hazard models calculating hazard ratios and 95% confidence intervals (CIs). Multivariate logistic regression will identify independent predictors, and linear or generalized linear models will assess the impact of ASPP and other factors on delivery outcomes and the ASQ-3 results. First, logistic regression will calculate odds ratios and 95% CIs for recurrent stroke. Subgroup analysis will evaluate potential differences in endpoints for predefined subgroups (such as gestational hypertension, preeclampsia, HELLP syndrome, gestational diabetes, trimester, and type of delivery). Multiple imputation will address missing baseline data, with a *p*-value of < 0.05 considered statistically significant.

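### The Aim 1 sample size is calculated for 1:3 matching (268/804) but the design is 1:1 (400/400), and under a two-sided odds-ratio reading neither gives 80% power for a 1.45-fold association

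*Protocol article*

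**What the plan says.** Sample size estimates (protocol article, Methods) takes its effect size from a Chinese women's cohort "reporting a 1.45-fold stroke risk increase with high parity (≥ 5 pregnancies"). From this it derives the Aim 1 requirement: "we calculated a requirement of 268 ASPP cases and 804 matched controls (1:3 ratio) to detect similar associations", at alpha 0.05 and 80% power. The paragraph ends with a different number: "Our target enrollment of 400 ASPP patients balances statistical rigor and feasibility, accounting for a 20% attrition rate".

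The design is fixed elsewhere. The matching criteria under Participating centers and patient population say that for the pregnant or postpartum non-stroke group "controls will be matched to ASPP cases in a 1:1 ratio based on age (±2 years) and hypertension history". For the other comparison group they say "For the nonpregnant stroke group, a 1:1 matching strategy will be applied". The Design paragraph of the abstract gives the group sizes: "400 pregnant/puerperal participants without a stroke history and 400 nonpregnant/puerperal participants with a recent stroke", alongside 400 ASPP patients.

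On the test, Statistical analysis plans a 0.05 significance threshold and 95% confidence intervals (for example "logistic regression will calculate odds ratios and 95% CIs for recurrent stroke"). It names no one-sided test.

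**The concern.** The calculation and the design disagree within the same article. The calculation asks for 804 controls at three per case; the design supplies 400 stroke-free controls at one per case. The text moves from 268 to 400 cases without saying what power the 1:1 design has.

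The 268 also looks too small for an odds ratio of 1.45. If it is, 80% power is a property neither of the calculated design nor of the planned one. Identifying risk factors is the first stated aim, and this is the only power statement made for it. A reader who trusts it may take a null result for a moderate or uncommon exposure as evidence of no association when the study had little chance of detecting one.

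**Working it through.** **Inputs from the article.** Effect 1.45; alpha 0.05; power 80%; calculated size 268 cases and 804 controls (k = 3 controls per case); planned size 400 and 400 (k = 1).

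**Assumptions.** Two-sided test, because 95% intervals are planned and no one-sided test is named. 1.45 as an odds ratio, because this part is a case-control study of a rare event (the Background gives 30 per 100,000 pregnancies), where a 1.45-fold risk is close to an odds ratio of 1.45. Cases and controls treated as unmatched samples. The article gives no control exposure prevalence p0, so it was scanned from 0.5% to 99.5%.

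**Formulas.**
- Exposure in cases: p1 = 1.45·p0 / (1 + 0.45·p0)
- Pooled exposure: p̄ = (p1 + k·p0) / (1 + k)
- Cases needed: n = [1.960·√((1 + 1/k)·p̄(1 − p̄)) + 0.842·√(p1(1 − p1) + p0(1 − p0)/k)]² / (p1 − p0)²
- Power: Φ{[|p1 − p0|·√n − 1.960·√((1 + 1/k)·p̄(1 − p̄))] / √(p1(1 − p1) + p0(1 − p0)/k)}

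**Step 1: try to reproduce 268 at 1:3.** The requirement is smallest near p0 = 0.44. There p1 = 0.638/1.198 = 0.5326, p̄ = 0.4631 and p1 − p0 = 0.09255. Then n = (1.1285 + 0.4843)² / 0.09255² = 303.6, so 304 cases and 912 controls. No prevalence gives 268. Other standard formulas do not help: their minima are 302 (unpooled variance), 304 (arcsine), 305 (Wald on the log odds ratio) and 318 (continuity-corrected).

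**Step 2: the planned 1:1 design.** The minimum is near p0 = 0.45, where p1 = 0.5426 and n = 456.3, so 457 per group against 400 planned. McNemar pairs without within-pair correlation also give 457.

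**Step 3: power and detectable effect.**

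| Exposure in controls | Power, OR 1.45, 268/804 | Power, OR 1.45, 400/400 | Detectable OR, 80% power, 400/400 |
|---|---|---|---|
| 5% | 27.1% | 23.6% | 2.17 |
| 10% | 42.5% | 39.4% | 1.81 |
| 20% | 61.8% | 59.9% | 1.59 |
| 45% (about the best case) | 74.9% | 74.6% | 1.49 |

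Cases needed at 10% exposure are 710 (1:3) or 1098 (1:1); at 5%, 1314 or 2040.

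**Step 4: which assumptions do give 268?** Two were found.
- One-sided alpha 0.05 (1.645 in place of 1.960): at p0 = 0.29, n = 267.9; at p0 = 0.61, n = 266.4.
- Two-sided, with 1.45 as a ratio of exposure proportions (p1 = 1.45·p0): at p0 = 0.179, n = 267.4.

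**Step 5: does the ratio mismatch cost power?** Hardly. The effective size 1/(1/cases + 1/controls) is 1/(1/268 + 1/804) = 201 for the calculation and 1/(1/400 + 1/400) = 200 for the plan. The gap from 80% therefore comes from the 268 figure, not from replacing 1:3 by 1:1.

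**The case against.** The strongest reply is that the article states alpha 0.05 without sidedness and does not say how 1.45 enters the formula. With a one-sided 5% test, power peaks at 83.8% for 268/804 and 83.6% for 400/400. With 1.45 as a ratio of exposure proportions, 400/400 reaches 80% from about 18.4% exposed. If the authors used either reading, 268 was right on their inputs and the planned design is close to 80% too. This stands as a limit: a reader might infer that 80% is unreachable whatever the assumptions, and that is not so. Both readings are nonetheless less natural. A one-sided test sits badly with 95% intervals, and a stroke-risk ratio is not a ratio of exposure proportions in a case-control comparison.

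It is also fair that a journal article may leave prevalence and sidedness to the full protocol. Their absence is not the point here. The contradiction in ratio and the non-reproduction of 268 are.

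Four further inferences are tempting but unsupported:
- **The 20% attrition cuts the risk-factor comparison to 320 pairs.** Exposures are baseline data from medical records, with telephone interviews only for unrecorded items, and missing baseline data are to be imputed. Nothing says that loss to follow-up removes cases from this analysis.
- **Matching makes power worse.** The direction depends on which odds ratio is fixed. With 400 pairs, 45% exposed and a within-pair correlation of 0.2, McNemar power moves from 74% to 65% if the conditional odds ratio is 1.45, but to 83% if the marginal one is. The article does not say which applies.
- **High parity is an unsuitable anchor.** No document gives its prevalence in these women.
- **The two comparison groups could be pooled.** 400 against 800 would reach up to 85.8%, but the second group consists of stroke patients and cannot serve as stroke-free controls for stroke risk factors.

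**Conclusion.** The statement is wrong as written. The calculation describes a 1:3 study with 804 controls, the design is 1:1 with 400, and no power is given for the latter. Under a two-sided 5% test, 1.45 as an odds ratio and an unmatched approximation, 268 is 36 cases below the smallest possible 1:3 requirement (304), and 400 per group is 57 below the smallest 1:1 requirement (457). Power for an odds ratio of 1.45 is then at most about 75% in either configuration, and far less for uncommon exposures.

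The conclusion is conditional on that reading. It does not mean that the change from 1:3 to 1:1 weakened the study, nor that the target of 400, which the article justifies partly by feasibility, has to rise.

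**What to change.** In Sample size estimates, replace the 268/804 sentence with one for the actual design: 400 cases and 400 stroke-free pregnant or puerperal controls, matched 1:1. State sidedness and the assumed control exposure prevalence, and give the minimum detectable odds ratio at 80% power: about 2.17 at 5% exposure, 1.81 at 10%, 1.59 at 20% and 1.49 at 45% (two-sided 5%, unmatched approximation). Remove the claim of 80% power for a 1.45-fold association, or keep it only with the inputs that support it.

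The cost is one rewritten paragraph. Enrolment, matching and data collection do not change.

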### Participating centers and patient population

This study is based on the method of stratified selection of centers according to the “China Maternal and Child Health Development Report (2019).” This study plans to include 36 regional or subregional centers in 22 provinces of China that meet 3 criteria to ensure sufficient geographical representativeness, making it a national-level study. The 3 criteria are the incidence rate of ASPP (> 5 cases per 100,000 pregnancies), the minimum annual case volume (≥ 15 ASPP cases), and obtaining standardized stroke care certification. The distribution of the final cohort of 36 tertiary hospitals is strategic and can reflect geographical and socio-economic diversity. Sample allocation uses adaptive quota sampling and is adjusted quarterly. The enrollment targets of each center are dynamically redistributed according to the real-time recruitment rate to maintain balance among the centers. All the above centers were selected based on voluntary participation. The geographical distribution of centers participating in the ASPP study is illustrated in Fig. 1.

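### The recurrence aim is said to need 456 ASPP cases for 90% power, but the target is 400 enrolled, about 320 after the stated 20% attrition, and no power is given at either size

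*Protocol article*

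**What the plan says.** Recurrent stroke is the primary outcome for Aim 2 (Primary outcome). Under Sample size estimates, the requirement for that aim reads: "456 ASPP cases are needed to identify a 40% risk reduction (90% power), anchored to China-specific stroke incidence data". The following sentence fixes the size of the study: "Our target enrollment of 400 ASPP patients balances statistical rigor and feasibility, accounting for a 20% attrition rate". It goes on to cite "multicenter recruitment capacity (36 centers, ~ 11 cases/center/year" and subgroup analyses as further considerations. The section gives no power for recurrence at 400, none after attrition, and no revised detectable effect.

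The Abstract plans 400 nonpregnant stroke participants as one comparator, and Participating centers and patient population matches them 1:1 to the ASPP cases. That section also sets a center criterion on volume: "the minimum annual case volume (≥ 15 ASPP cases" per center. Inclusion runs from January 2015 to November 2024.

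**The concern.** Allowing for attrition makes an enrollment target larger than the number needed for analysis. Here the target is smaller than the stated requirement before any loss, yet attrition is said to be accounted for. A reader looking for the power of the recurrence analysis finds only 90%, attached to a sample that the study does not plan to recruit. If Aim 2 shows no difference, that result may be weighed against a power figure that the planned size does not reach. The capacity figure does not explain the gap either: read literally, the centers could supply the missing 56 cases in about two months.

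**Working it through.** **Inputs.** From Sample size estimates: 456 cases, a 40% risk reduction (taken as a ratio of 0.60), 90% power, 400 enrolled, 20% attrition, 36 centers, about 11 cases per center per year. From Statistical analysis: "value of < 0.05 considered statistically significant". Sidedness is not restated for the 456 calculation, so two-sided 5% is assumed and one-sided was also tried.

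**Can 456 be reproduced?** Not forward. The comparator recurrence risk is not given as a number (the source is described only as "anchored to China-specific stroke incidence data"), and the comparison and sidedness are not stated. Working backward with the usual two-proportion formula, n = [1.960·√(2p̄(1−p̄)) + 1.282·√(p₁(1−p₁)+p₂(1−p₂))]² / (p₁−p₂)² with p₂ = 0.6·p₁, n = 456 per group corresponds to p₁ = 19.4% and p₂ = 11.6%. That is an implied value, not one found in the article. The steps below do not need it.

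**Shortfall.**
- 456 − 400 = 56 (12.3% of 456).
- 400 × 0.8 = 320, and 456 − 320 = 136 (29.8% of 456).
- Enrollment needed for 456 evaluable: 456 / 0.8 = 570.

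**Power scaled from 456 and 90%.** The standardized effect at 456 is 1.960 + 1.2816 = 3.2415, and it scales with √(n/456).
- n = 400: 3.2415 × √(400/456) = 3.036; Φ(3.036 − 1.960) = 85.9%.
- n = 320: 3.2415 × √(320/456) = 2.716; Φ(2.716 − 1.960) = 77.5%.

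**Sensitivity to the unstated choices.**

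| Method | 400 evaluable | 320 evaluable |
|---|---|---|
| Two proportions, two-sided, 1:1 | 85.9% | 77.5% |
| Two proportions, two-sided, 1:3 | 86.2% | 78.5% |
| Two proportions, one-sided, 1:1 | 86.3% | 79.0% |
| Schoenfeld, hazard ratio 0.60 (162 events at 456) | 86.1% | 77.7% |
| Freedman, hazard ratio 0.60 (169 events at 456) | 86.1% | 77.7% |

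**If 456 already includes attrition.** The evaluable requirement is then 456 × 0.8 = 364.8, or 380 if 456 was obtained as 380 × 1.2. With 320 evaluable, power is Φ(3.2415 × √(320/364.8) − 1.960) = 85.9% or Φ(3.2415 × √(320/380) − 1.960) = 84.5%.

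**Capacity.**
- 36 × 11 = 396 per year. January 2015 to November 2024 is 119 months, so 396 × 119/12 = 3,927 cases.
- 400 / 36 = 11.1 cases per center over the whole window, and 11.1 / (119/12) = 1.1 per year.
- 56 / 396 = 0.14 years, or 1.7 months of recruitment at the stated rate.

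**The case against.** The strongest reply is that the article attaches 90% to 456 and openly presents 400 as a compromise between rigor and feasibility. A reader might infer that it claims 90% power at 400; it does not say so. Accounting for attrition could also mean only that attrition was weighed. This stands as a limit on the point: the defect is a requirement, a target and an attrition statement left unreconciled, not a false claim of 90% at 400. It does not remove the point, because no other power is given for a primary outcome.

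Second, 320 is nearer a lower bound. Recurrence is also to be analysed by Kaplan-Meier and Cox methods, and women lost after an earlier contact still contribute follow-up. The article does not say when the 20% is lost. This also stands, and it is why both 400 and 320 are shown.

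Third, two readings would restore 90%. If 400 were evaluable and 456 enrolled, power would be about 92%, but the article calls 400 the enrollment target. If 456 covered both groups (228 each), 320 would exceed the need, but the article says 456 ASPP cases.

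Three stronger inferences are not supported:
- **That power is really far lower.** Comparator risks of 5% or 10% would give about 25% or 46% at 320 per group, but neither risk is in the article, and both conflict with the roughly 19% implied by 456.
- **That incidence was used where recurrence was needed.** The phrase may loosely describe recurrent events, and a condensed article does not show the calculation.
- **That the capacity figure is wrong by a known factor, or contradicts the center criterion.** The total of 11.1 per center makes a unit slip plausible, but the article does not show which number is wrong. About 11 recruitable patients is compatible with at least 15 seen, given consent and exclusions.

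**Conclusion.** The point holds in this limited form. The requirement of 456, the target of 400 and the 20% attrition cannot be reconciled as written, and the only power stated for Aim 2 is not what the chosen size supports. The loss is moderate: from 90% to about 86% if all 400 are evaluable, and to about 77–79% if 320 are. If 456 already contains the attrition allowance, power is about 84–86%. These figures take 456 at 90% as correct, which cannot be verified. They also assume that information falls in proportion to the number of evaluable cases. The shortfall in case numbers needs neither assumption. The capacity figure is a separate inconsistency: as printed, it is about ten times the target over the inclusion window and so gives no reason for a target below 456.

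**What to change.** In Sample size estimates:

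1. State the Aim 2 power, or the detectable effect, at 400 enrolled and at about 320 evaluable. Give the inputs used: the comparator recurrence risk, alpha and sidedness, and which groups are compared. Say whether 456 is an enrolled or an evaluable number.
2. Remove or correct the statement that 400 accounts for 20% attrition.
3. Reconcile the capacity of about 11 cases per center per year with a total of 400, about 11 per center overall. Clarify the unit, and say how capacity led to a target below 456.

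This changes wording only, with no change to data collection, and the price is a less favourable stated power. If the sponsor prefers to keep 90% with 456 evaluable, the route is 570 enrolled ASPP cases, which does carry a recruitment cost.

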The findings of this study should be interpreted within the context of potential limitations. Firstly, this is a retrospective study, which is subject to several inherent biases, such as recall and information bias, potentially jeopardizing its validity. Secondly, follow-up via telephone interviews may lead to a high dropout rate. Thirdly, concerns among ASPP patients regarding the privacy of their offspring’s information may result in a significant number being unwilling to cooperate, leading to selection bias. To address these issues, expanding the sample size by including more centers would be an effective solution for achieving statistical validity. Finally, although this study focuses on the Chinese population and mainly includes the Han ethnic group as the primary ethnic cohort, it employs two methodological measures, geographical heterogeneity and biological consistency, to ensure the generalizability of the research findings. The study included 22 provinces representing different socio-economic and medical resource conditions to ensure geographical heterogeneity. According to previous national studies, in the Chinese population, the key risk factors for ASPP, such as hypertension and coagulation dysfunction, show minimal differences across different ethnic groups, suggesting that the study subjects have biological consistency [24, 25].

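### For recurrence (Aim 2), the target of 400 ASPP patients is below the plan's own requirement of 456 and does not cover the stated 20% attrition; the achieved power is not given

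*Protocol article*

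**What the plan says.** The paragraph under Sample size estimates contains two calculations and one target.

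- Aim 1 (risk factors): 268 ASPP cases and 804 controls, alpha 0.05, 80% power.
- Aim 2 (recurrence): "456 ASPP cases are needed to identify a 40% risk reduction (90% power), anchored to China-specific stroke incidence data". Neither the baseline recurrence rate nor the sidedness of the test is given.
- Target: "Our target enrollment of 400 ASPP patients balances statistical rigor and feasibility, accounting for a 20% attrition rate". The same sentence also cites recruitment capacity and subgroup analyses.

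The Abstract repeats the target ("planned to include 400 ASPP patients from 36 centers across 22 provinces in China") and plans 400 nonpregnant women with stroke as a comparison group. The Methods match that group 1:1 to the cases. Recurrent stroke is the primary outcome for Aim 2. The Follow-up schedule has three telephone rounds, the last ending in February 2031. The limitations in the Discussion warn that "follow-up via telephone interviews may lead to a high dropout rate" and suggest adding centers to enlarge the sample.

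**The concern.** A target that allows for attrition should exceed the evaluable number required. Here it is lower than that number, in the sentence directly after it. The paragraph gives no power for 400, no detectable effect at 400, and no statement that the recurrence requirement is unmet.

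Aim 2 is the analysis that the paragraph itself calls longitudinal, so loss to follow-up matters most there. If the recurrence comparison turns out non-significant, a reader who trusts the attrition statement would think dropout had been provided for. The chance of missing a true 40% reduction would then be judged smaller than it is.

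**Working it through.** **Inputs from the protocol article.** Required ASPP cases 456, power 90%, reduction 40% (ratio 0.6), target 400, attrition 20%, 1:1 matching, Aim 1 case requirement 268.

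**Assumptions.** Two-sided 0.05 (alpha is not restated for the 456 figure). The comparator is the nonpregnant stroke group, and it is the same size as the ASPP group at every step.

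**1. Can 456 be reproduced?** Not from the article, because the baseline recurrence rate is missing. Solving backwards with a two-proportion formula (ratio 0.6, 90% power, 1:1), 456 per group corresponds to 19.4% versus 11.6% two-sided, or 16.3% versus 9.8% one-sided. On a hazard-ratio scale, 0.6 with 90% power needs 162 events (Schoenfeld) or 169 (Freedman), and 162/912 = 17.8% and 169/912 = 18.5%. So 456 per group is attainable but cannot be verified. It is taken as given below.

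**2. Attrition.**
- Aim 2 before loss: 456 − 400 = 56 short; 400/456 = 87.7%.
- Aim 2 after loss: 400 × 0.8 = 320; 456 − 320 = 136 short; 320/456 = 70.2%.
- Enrolment that would cover the loss: 456/0.8 = 570.
- Aim 1 case count: 268/0.8 = 335, which is below 400, so the statement holds there.

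**3. Power against the same 40% reduction.** Scaling the noncentrality needs no baseline rate:

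Power(n) = Φ[(1.960 + 1.2816) × √(n/456) − 1.960]

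- n = 400: Φ(3.2416 × 0.9366 − 1.960) = Φ(1.076) = 85.9%
- n = 320: Φ(3.2416 × 0.8377 − 1.960) = Φ(0.756) = 77.5%

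A direct two-proportion calculation at 19.4% versus 11.6% gives 85.9% and 77.4%. One-sided, the scaled figures are 86% and 79%.

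**4. Other readings of the two numbers.**
- 400 is what remains after attrition: still below 456, power 85.9%.
- 456 already includes attrition (456 × 0.8 = 365 evaluable): 320 evaluable gives Φ[3.2416 × √(320/364.8) − 1.960] = 85.9%.
- 456 is the total over both groups (228 each): 320 per group would give about 97%. The text says ASPP cases, so it does not support this reading.

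**5. Sensitivity if 456 itself is wrong.** Two-sided, 1:1, ratio 0.6, with assumed comparator recurrence:

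| Comparator recurrence (assumed) | n per group for 90% | Power at 400 | Power at 320 |
|---|---|---|---|
| 10% | 965 | 55% | 46% |
| 15% | 615 | 74% | 65% |
| 20% | 440 | 87% | 79% |
| 25% | 335 | 94% | 89% |

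The true figure depends strongly on a rate the article does not report.

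**The case against.** The strongest reply is that the plan never claims 90% power for 400. It ties that figure to 456 and presents 400 as a compromise with feasibility, with both numbers in plain view. That is correct. A reader might infer a broken promise of 90% power at the enrolled number, and the text does not support that. What remains is narrower: attrition is described as accounted for, and no power is given for 400.

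A second reply is that accounting for attrition may mean only that it was considered, alongside recruitment and subgroups. Even so, the statement is literally true for the Aim 1 case count and untrue for Aim 2, and the sentence does not separate them. It should be qualified by aim rather than deleted.

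Third, the Statistical analysis section names log-rank and Cox methods, under which a woman lost to follow-up contributes time until censoring. Treating her as wholly absent is conservative, so 77–78% is a lower bound. The 20% is also stated only beside the ASPP target. If the comparator lost fewer, power would lie between the two figures. Neither point restores 90%, because 400 with no loss gives about 86%.

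Fourth, the Discussion admits the dropout risk and names more centers as a response. That is candid, but it does not close the gap between 400 and 456.

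Harsher calculations are tempting and should be resisted. A reader might count only matched pairs in which both members are retained, but the Statistical analysis section names no paired method. A reader might compound 20% over the three rounds, but the plan gives one overall rate and none per round. A reader might quote a single reduction detectable at 90%, but that needs a baseline rate the article does not give.

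**Conclusion.** The point holds for Aim 2. By the plan's own numbers, 400 is 12% below the recurrence requirement before loss (56/456) and 30% below it after the stated 20% loss (136/456). Power for the 40% reduction is about 86% if all are evaluable and about 77–78% at 320, so the chance of missing that effect rises from 10% to roughly 14–22%.

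This rests on 456 being correct at exactly 90% power and two-sided 0.05, and on a comparator of proportional size. The 456 cannot be checked. That 400 falls short of 456 depends on none of these assumptions. The shortfall is moderate and does not invalidate the study; what is wrong as written is the unqualified attrition statement and the missing power for 400.

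**What to change.** Keep 400 and revise the sample size paragraph:

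1. Restrict the attrition statement to the Aim 1 case count (268/0.8 = 335, within 400).
2. State that the Aim 2 requirement of 456 is not met: 400 enrolled, about 320 if 20% are lost.
3. Replace the 90% for Aim 2 with the achieved power, about 78% to 86% on the stated inputs, or with the reduction detectable at 90%. Compute it from the sponsor's own baseline recurrence rate.
4. Report that rate, the sidedness of the test and the comparator size behind 456, so that the figure can be checked.

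The cost is a few sentences and a less favorable power statement. The alternative of enrolling about 570 would restore the 90% with attrition covered, but it is not needed to make the text correct.

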**Fig. 1 Fig1:**
[figure not shown]
The geographical distribution of centers participating in the ASPP study. The ASPP study aims to include 36 territorial or regional centers across 22 provinces in China

ASPP patients and non-ASPP participants from January 2015 to November 2024 will be included (Fig. 2). Table 1 lists the inclusion criteria and exclusion criteria. ASPP patients are defined as those who experience acute stroke events during pregnancy or within 6 weeks postpartum, confirmed by neuroimaging evidence of cerebral infarction or hemorrhage corresponding to their symptoms.

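### The capacity of about 11 cases per center per year does not justify stopping at 400 over a ten-year case window, and a rate-driven quota is poorly suited to strokes that have already occurred

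*Protocol article*

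**What the plan says.** - **Target.** Sample size estimates: "Our target enrollment of 400 ASPP patients balances statistical rigor and feasibility". The same section says that the recurrence analysis needs 456 ASPP cases (40% risk reduction, 90% power). It names 20% attrition, subgroup analyses and a recruitment capacity of 36 centers at about "11 cases/center/year" as the considerations behind 400.
- **Case window.** Participating centers and patient population: "ASPP patients and non-ASPP participants from January 2015 to November 2024 will be included". The Abstract (Design) agrees: "planned to include 400 ASPP patients from 36 centers across 22 provinces in China, from 2015 to 2024".
- **Center criterion.** Participating centers and patient population requires, among other things, "the minimum annual case volume (≥ 15 ASPP cases").
- **Allocation.** The same section describes an adaptive quota revised every quarter, with center targets "dynamically redistributed according to the real-time recruitment rate to maintain balance among the centers".
- **Consent.** Table 1 makes consent from the patient, a representative or a relative an inclusion criterion, and missing key baseline data an exclusion. The Discussion concedes that unwillingness to cooperate may cause selection bias and offers more centers as the answer.

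**The concern.** The capacity figure helps to justify a target that lies below one of the plan's own requirements. If the capacity really is annual, the 2015–2024 window holds several times the number of cases needed, and feasibility is no reason to stop at 400. If the figure is a total per center with the wrong time unit, it sits oddly with a criterion that admits only centers seeing at least 15 cases a year. In both cases a reader cannot tell how many cases were available or why 400 was chosen.

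The second part is how the 400 are reached. Every qualifying stroke has occurred by the end of November 2024. In a closed set of past cases, the speed of enrollment depends on caseload, but also on how easily women are traced, how readily they consent and how quickly a center abstracts records. Targets that follow that speed can tie inclusion to factors related to outcome: women who have died, are disabled or have moved are harder to reach. Recurrence, mortality and functional outcome could then differ from those of ASPP patients at these centers as a whole.

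**Working it through.** **Inputs**
- Target: 400 cases; recurrence requirement: 456; attrition: 20% (Sample size estimates).
- Centers: 36; stated capacity: about 11 per center per year (Sample size estimates).
- Criterion: at least 15 cases per center per year (Participating centers and patient population).
- Window: January 2015 to November 2024 = 119 months; 119/12 = 9.92 years.

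**1. Reproducing 400.** Centers × rate = 36 × 11 = 396, and 400/36 = 11.1 per center. The target is recovered only when the time dimension is dropped or set to one year.

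**2. The stated rate over the stated window.** 36 × 11 × 119/12 = 3,927. This is 3,927/400 = 9.8 times the target. Using 9 or 10 years changes it only to 3,564 or 3,960.

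**3. What 400 means when spread over the window.** 400/(36 × 9.92) = 1.12 per center per year.

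**4. The center criterion over the window.** 36 × 15 × 119/12 = 5,355 cases seen, as a minimum if the criterion held in every year. In a single year it gives 36 × 15 = 540, already above both 400 and 456.

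**5. Share taken.**

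| Annual rate per center | Cases over 9.92 years | 400 as a share |
|---|---|---|
| 11 | 3,927 | 10.2% |
| 15 (minimum) | 5,355 | 7.5% at most |

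These are shares of all cases at those rates, before exclusions and consent. The documents give no yield. If 50%, 25% or 10% of the 5,355 were eligible, consenting and complete (assumed range), 400 would be 15%, 30% or 75% of them.

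**6. Does capacity stand in the way of 456?** At 396 a year, 456 takes 456/396 = 1.15 years of case accrual. Inflated for 20% attrition, 456/0.8 = 570, which takes 570/396 = 1.44 years. The window is 9.92 years.

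**7. Plausibility of the annual figures.** The Background gives an incidence of 30 per 100,000 pregnancies. Fifteen cases a year then correspond to 15/30 × 100,000 = 50,000 pregnancies a year behind each center. Referral could explain this, but the article does not say so.

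**The case against.** The strongest reply is that the figures measure different things.

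- **11 against 15.** A reader might infer that a center with 11 cases a year fails the criterion of 15. The documents do not support that. The 15 is a volume of cases seen; the 11 is described as recruitment capacity. Enrolling 11 of 15 (73%) after consent and the Table 1 exclusions is possible, though the article does not say that this is meant. This reply stands.
- **11 per year against 400.** Enrollment work in a retrospective study can run on its own clock. One year of it gives 396, so a strict contradiction is not proven. This also stands, and it means that relabelling the figure as a total per center would only be a guess. But the article states no enrollment period, and under this reading 400 is still drawn from a decade of cases.
- **Over 90% of eligible cases left out.** A reader might take this from the shares above. It does not follow: it needs 15 a year at every center throughout the window, and it counts cases seen as if all were eligible.
- **Quota moves to fast centers.** The article gives no direction for the movement and names balance as its purpose. Only the dependence on recruitment rate is stated.
- **Consent selects women under any rule, and the Discussion admits it.** True, but adding centers does not remove that selection, and a rule tied to enrollment speed can add to it.
- **Capacity is one of several considerations, and an article condenses.** Also true: 400 is not computed from the 11. But the figure, the window, the criterion and the quota rule are all printed, so the difficulty is not one of omitted detail.

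**Conclusion.** The point holds in a limited form. Over the window that the article states, a capacity of about 11 cases per center per year yields some 3,927 cases. It agrees with 400 only as a total per center or as one enrollment year. As printed, it does not justify stopping at 400, 56 below the 456 required for recurrence. Whether the 11 is a wrong unit or an unexplained enrollment year cannot be settled from the article.

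If the annual figures are right and held throughout, 400 is roughly 7–10% of cases seen, and a larger but unknown share of those who are eligible and consent. If they are too high, that share rises and the center criterion itself needs correcting.

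Allocating a closed set of past cases by recruitment rate carries a risk of selection bias whose size and direction the documents do not allow one to estimate. It does not by itself defeat the claim of geographical representativeness, which concerns the spread of centers.

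**What to change.** 1. In Sample size estimates, state what the 11 counts (cases seen or cases that can be enrolled) and over what period. Reconcile it with the 15-per-year criterion, the 2015–2024 window and the 456.
2. Restate the reason for 400 and give the power that it delivers for the recurrence aim after the stated attrition, or raise the target.
3. Replace the rate-driven quota with a fixed rule. Each center lists all qualifying ASPP admissions from January 2015 to November 2024. It then approaches all of them, or a random sample stratified by year with a target proportional to its list. Targets do not move with recruitment speed.
4. Report listed, approached and enrolled counts by center, so that the yield and any selection can be seen.

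**Cost.** A corrected figure and a change of protocol wording. Each center must draw up a list, which could be long if the annual volumes are right (15 × 9.92 ≈ 149 cases per center), and some centers may fill their allocation more slowly.
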